### 2.3. Sample size

From the 4 factors needed to calculate sample size (i.e., significance level, power, difference between groups, and standard deviation), 2 are unknown (difference between groups and standard deviation) because no previous study used HRV for older adults. Although pilot randomized controlled trials do not require sample size calculations, 15 to 20 participants per group would be necessary to ensure validity. Therefore, we will include 100 participants, 50 participants per group. Our results will provide the information necessary for sample size calculation in future studies.

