#### 2.6.2. Data collection related to the primary aim (HRV) and (body composition).

HRV will be assessed at rest and during exercise using the Polar V800. The Polar V800 is a heart rate monitor that captures electrical impulses from the heart. A device similar to a watch will be placed on participants’ left wrist, and a chest strap with a capture sensor will be positioned on their xiphoid process.

The assessment at rest will describe participants’ cardiac autonomic profile. Participants will be quiet and rest in supine position for 20 minutes in an air-conditioned room (22°C–25°C).

The assessment during exercise will be completed in 2 moments: pre- and post-intervention. The cardiac responses to the different phases of the exercise (i.e., 5-minutes warm-up, 30-minutes aerobic training, 20-minutes strength training of peripheral muscles, and 5-minutes relaxation) will be observed. EG will complete a physical exercise protocol validated by Raimundo et al,^[8]^ and GG will perform gametherapy (Just Dance 2013) Marques et al.^[9]^

HRV will be measured at rest and during exercise using linear methods in the time and frequency domains, non-linear methods, and Poincaré graph. Data analysis will be based on the heart rate recorded during the protocol, and only time series with more than 95% of sinus beats will be used for analysis. After checking for errors, a trace will be selected for analysis and filtered using the Polar Precision Performance SW software (version 4.01.029). Analysis will be performed using the Kubios software.^[9]^

Body composition will be assessed using electrical bioimpedance. Participants will be fasting for 2 hours, with empty bladder (used the bathroom 30 minutes before), and will not have practiced physical activity in the previous 8 hours. OMRON equipment (model HBF-514) will be used; the equipment is composed of a tetrapolar system with 8 electrodes that transmit an extremely low electric current of 50 kHz and 500 µA. Six variables will be recorded: basal metabolism value, body fat percentage, skeletal muscle percentage, body mass index, visceral fat percentage, and basal metabolic rate.

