### 2.12. Statistical analysis

Baseline measures between groups will be compared. The distribution of continuous quantitative variables will be tested for normality and graphically inspected using histograms. A general linear model will analyze differences between groups for the primary and secondary outcomes. If normality assumption is not met, we will proceed with non-parametric techniques (i.e., quantile regression). Effect size (95% confidence interval) and level of statistical significance will be displayed. Missing data will be replaced using multiple imputations. We will minimize potential confounding by adjusting baseline values and controlling other potential confounders. Statistical significance will be set at *P* < .05.

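### A normality pre-test, apparently on raw variables, decides whether an HRV index is analysed as a mean or a quantile difference; the cost in precision depends on skewness the protocol does not give

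*Protocol article*

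**What the plan says.** Section 2.12 sets out a sequence. First: "The distribution of continuous quantitative variables will be tested for normality and graphically inspected using histograms". Next: "A general linear model will analyze differences between groups for the primary and secondary outcomes". Then the switch: "If normality assumption is not met, we will proceed with non-parametric techniques (i.e., quantile regression"). The same section plans covariate adjustment: "We will minimize potential confounding by adjusting baseline values and controlling other potential confounders".

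It does not name the normality test, the quantile, or whether the switch is made variable by variable. It mentions neither residuals nor a transformation.

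HRV is part of the primary outcome. Section 2.6.2 describes it by families of measures: "HRV will be measured at rest and during exercise using linear methods in the time and frequency domains, non-linear methods, and Poincaré graph". No distribution, skewness or SD is given for any index.

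**The concern.** A linear model adjusted for baseline relies on roughly normal residuals, not on normal raw variables. A raw variable can fail a normality test while the residuals are acceptable, and the reverse can happen. A check on the variables can therefore trigger the change of method for the wrong reason.

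The change is also more than technical. The linear model estimates a difference in means and quantile regression a difference in some quantile, so the pre-test result chooses the quantity reported. Several related HRV indices come from the same recording. If the rule is applied to each, some could end up with one target and some with the other. Section 2.3 expects the results to feed later sample size calculations, which is harder when the target is settled only after the data are seen.

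Precision is also at stake. If an index is skewed in a way that logarithms would largely remove, median regression discards information that a log-scale linear model would keep.

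**Working it through.** The protocol gives no power, efficiency or detectable difference for this analysis, so there is no figure to reproduce.

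**Inputs from the protocol**
- Size: "Therefore, we will include 100 participants, 50 participants per group" (section 2.3).
- Significance: "Statistical significance will be set at *P* < .05" (section 2.12); two-sided testing is assumed.
- Of the quantities needed for a sample size, "2 are unknown (difference between groups and standard deviation) because no previous study used HRV for older adults" (section 2.3).

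**Assumptions, not in the protocol**
- The index is log-normal, with log SD s between 0.2 and 1.0.
- The normality test is Shapiro-Wilk at 5%.
- The quantile is the median.
- The power target is 80%.

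**1. How often the switch would be triggered** (2,000 simulated samples per cell)

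| Log SD | 0.2 | 0.3 | 0.4 | 0.5 | 0.7 |
|---|---|---|---|---|---|
| N = 100 | 54% | 88% | 98.5% | 99.95% | 100% |
| N = 50 | 31% | 55% | 79% | 92% | 99% |

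At N = 100 the switch is near certain from log SD of about 0.4, and close to a coin toss at 0.2.

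**2. Loss against a linear model on the log scale**

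With normal log-scale errors, the efficiency of quantile regression at quantile τ is φ(z_τ)² / [τ(1 − τ)]. At the median this is 0.3989² / 0.25 = 2/π = 0.637, a loss of 1 − 0.637 = 36%. In information, 100 participants count as about 64, and about 100 / 0.637 = 157 would be needed to make up the loss.

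**3. Range of that loss**
- Baseline-adjusted simulation, 50 per group, 600 to 800 runs, baseline correlation 0 or 0.6: relative efficiency 0.59 to 0.69 at log SD 0.4 and 0.7 (loss 31% to 41%), and 0.49 to 0.59 at log SD 1.0 (loss 41% to 51%).
- Heavier-tailed log-scale errors: t with 20, 10 and 5 degrees of freedom gives losses of 31%, 24% and 4%.
- Another quantile: at τ = 0.25 with normal errors, the loss is 46%.

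**4. Cost of the switch against the model actually planned**

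On the printed wording the planned model is linear on the raw scale. For small effects its efficiency against the log scale is s² / (exp(s²) − 1). The cost of switching is 1 − 0.637 / that efficiency.

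| Log SD | Raw-scale efficiency | Cost of switching |
|---|---|---|
| 0.4 | 0.16 / 0.1735 = 0.92 | 31% |
| 0.6 | 0.36 / 0.4333 = 0.83 | 23% |
| 0.9 | 0.81 / 1.2479 = 0.65 | 2% |

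At log SD 1.0 the raw-scale efficiency is 0.58, below 0.637, so the switch would gain a little. The simulation shows the same pattern. At log SD 0.4, median against raw-scale linear is 0.694 / 0.925 and 0.626 / 0.847, a cost of 25% to 26%. At 1.0 it is 0.594 / 0.547 and 0.490 / 0.420, a gain.

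**5. Detectable difference and power, in residual-SD units**

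With 50 per group: (1.960 + 0.842) × √(2/50) = 0.56. With 50 × 0.637 = 31.8 per group: 2.802 × √(2/31.8) = 0.70. The ratio is √(π/2) = 1.25. At a true difference of 0.566 the power falls from 81% to 62%. In the simulation, at 0.56, power was 0.77 to 0.81 for the log-scale model and 0.49 to 0.61 for raw-scale median regression. Part of that gap arises because the median test was conservative there (type I error about 0.03).

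**The case against.** The strongest reply is that the 36% uses a benchmark the protocol does not plan. Measured against the raw-scale linear model, the switch costs much less as skewness grows and nothing at the top of the range. This stands, which is why both comparisons are shown.

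A second reply is that an article may leave scale and transformation to an analysis plan, and nothing printed forbids logarithms. A missing transformation alone would indeed be no finding. But section 2.12 states a rule: test, fail, change to quantile regression. A later plan that kept the rule would keep the problem, and one that inserted a log step would be changing the rule.

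Third, the sentence on the switch follows the linear model sentence, so the assumption meant could be the model's own, on residuals. That reading is possible. The only check described, however, is on the variables, and a switch based on residuals would still let the data choose the target.

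Fourth, baseline-adjusted quantile regression is a legitimate method, and logarithms bring their own mix of ratios and mean differences across outcomes. Both are true. The difference is that the mix would be fixed in advance.

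Some stronger readings go beyond the text:
- A reader might infer that the HRV indices will all go to median regression and lose a third of the information. The protocol gives no distribution, test or quantile, and pairs the test with histograms, so an automatic switch cannot be presumed.
- A reader might infer that effects would not be comparable between visits. Nothing says the switch is made visit by visit.
- A reader might fault quantile regression for ignoring the two periods per participant. An ordinary linear model ignores them too, so that is a separate question.

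**Conclusion.** The point holds in conditional form. Section 2.12 lets a normality check, apparently on raw variables, decide whether a primary HRV index is summarised by a mean or a quantile difference. That weakness does not depend on any efficiency figure.

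The size of the loss does. It rests on log-normal indices and the median as the quantile, neither of which the protocol states. Under those assumptions the central figure is 36% against a log-scale model, equivalent to a detectable difference about 1.25 times larger in residual-SD units. The cases tried run from about 4% (heavy-tailed log errors) to about 51% (log SD 1.0). The cost of the switch alone is highest for moderate skew and close to nil by log SD 0.9. The headline 36% should therefore not be quoted as what this trial will lose.

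**What to change.** Reword section 2.12, before outcome data are examined, to say that:
- positive HRV indices expected to be right-skewed are listed in advance and analysed on the natural-log scale in the planned baseline-adjusted model, with results as ratios of geometric means and 95% confidence intervals;
- model residuals are checked, not the raw variables;
- if residuals are clearly non-normal, the model is kept and robust or bootstrap intervals are used;
- quantile regression, with the quantile named, is a sensitivity analysis only.

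The cost is a few sentences, with no change to design, sample size or data collection. The small downside is that these HRV effects are reported as ratios while other outcomes remain mean differences.

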### 2.13. Registration and adherence to SPIRIT standards

This study was prospectively registered in the ISRCTN registry (ISRCTN27697878) on October 4, 2019, before participant enrollment (i.e., October 15, 2019). This study will follow SPIRIT guidelines for randomized clinical trials, and results will be reported following 2010 CONSORT standards (http://www.consort-statement.org/).

## 3. Discussion

Our study will evaluate the effects of an evidence-based and supervised exercise protocol on active older adults. This study will allow translating exercise-based research into clinical practice. There is a paucity of studies regarding exercise in active older adults. Therefore, some of our study criteria will be defined based on populations other than older adults. We completed a 2-week pilot study to evaluate the exercise protocol and test its feasibility in individuals with different characteristics.

If the proposed protocol does not have the expected beneficial effect on HRV, results of this clinical trial will still be interesting to science. If we find unexpected results, this study will contribute to new ideas and research hypotheses, such as modifying the exercise protocol, combining it with other interventions (e.g., nutritional or psychological treatments), or increasing the follow-up period. We will prepare our results for submission to conferences, journal publication, and other sources without restrictions. Participants will receive personal information on their results and a summary of overall results.

### 3.1. Limitations/study risks and contingency plan

Potential risk 1: EG participants not attending to intervention sessions.

Contingency plan: Different strategies will be implemented to maximize adherence to the exercise protocol. The emotional state (The Feeling Scale) will be monitored, and any adverse events will be registered during training to understand participants’ feelings and implement adaptations. Participants will also receive motivational messages via WhatsApp every week and motivational videos from coaches and the research team at the beginning of each month.

Potential risk 2: Low recruitment and/or retention rate.

Contingency plan: The research team will invite as many active older adults to participate as possible. If the recruitment rate is still low, we will reach out to other exercise training facilities in different areas to recruit potential participants.
